## Methods

### Project objectives

To achieve the central goal of supporting sustained implementation of *Turtle Island Tales* through community-informed CEDI strategies, the aims of this project include (1) supporting and evaluating the reach of *Turtle Island Tales* when delivered through Extension/SNAP-Ed in Native American communities experiencing persistent poverty, (2) evaluating the capacity of state-level Extension and SNAP-Ed systems to adopt, implement, and sustain the program over time, (3) determining the short- and long-term budget impact of integrating *Turtle Island Tales* into routine program delivery, and (4) capturing the different implementation strategies used across implementing sites and the dynamic changes made to strategies within and across each site over the course of program delivery.

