### Study design and setting

This multilevel participatory action research project will use a descriptive case study methodology across four state SNAP-Ed programs that will be engaged to facilitate the dissemination, implementation, and sustainability potential of *Turtle Island Tales*. In many states, Cooperative Extension programs of land-grant universities serve as SNAP-Ed implementing agencies; therefore, we will engage partners working within both systems. CFIR and RE-AIM will be integrated to systematically address implementation barriers and promote the co-creation of sustainable dissemination strategies, with reach as the primary outcome. A convergent mixed methods approach will combine quantitative assessments related to predictors from the CFIR and RE-AIM outcomes with qualitative data to better characterize the planning, execution, and evaluation of CEDI strategies.

This project will be conducted in SNAP-Ed systems across four states: Montana, Oregon, South Dakota, and Wisconsin. All participating census tracts are rural, with 43% classified as frontier. Local SNAP-Ed agents and Native American community partners will lead the implementation efforts, focusing on state-specific community partnerships with reservation-based Native American communities. We anticipate that each Community Implementation Team will include local SNAP-Ed agents, tribal partners, and other community representatives. Figure 1 outlines the five-year, staggered implementation and evaluation timeline for *Turtle Island Tales* across four planned states. Under the guidance of the shared Project Steering Committee, Montana and South Dakota will begin with pre-implementation work in Year 1, followed by facilitated implementation with 50 families per state. Implementation capacity in these state systems will be assessed in Year 2, followed by community sustainability evaluation in Year 3. After the initial implementation year, we will track scale-out to additional communities within each state. Wisconsin and Oregon start pre-implementation work in Year 1, begin facilitated implementation in Year 2, and proceed through the same phased evaluation process in Years 3 to 5. Key evaluation outcomes, aligned with the RE-AIM framework, are embedded throughout all phases.

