Multi-leveled engagement with advisory boards, members from the population intended to benefit, and previous family participants	Academic & community partners, champions, decision makers & doers	Collaborative planning, development, and evaluation of a culturally relevant, family-based obesity prevention intervention	Native American families	Research question and intervention development, testing, and interpretation of results	Monthly advisory board meetings, 36 months; five focus groups with program participants; two randomized controlled trials	*Intervention Characteristics*; source, cultural compatibility, relative advantage, complexity	Reach, Effectiveness, Adoption, Implementation, Maintenance (individual and program)
Co-production, intervention packaging, and developing a formal implementation blueprint	Native American Communities, Research Team, CITs	Collaborative development of culturally relevant, family-based obesity prevention intervention	Native American families	Intervention development, testing, and interpretation of results	Within monthly CIT meetings; use of blueprint across facilitation strategies	*Intervention Characteristics*; source, cultural compatibility, relative advantage, complexity; design quality and packaging	Reach, Effectiveness, Adoption, Implementation, Maintenance (individual and program)
Centralize distribution and technical assistance (dissemination organization)	Research Team	Distribute *Turtle Island Tales* to families recruited in local communities	SNAP-Ed providers; other community implementors	During implementation, Sustainment, Scale-out	Monthly; technical assistance as needed	*Intervention Characteristics*; design quality and packaging *Implementation Process*; Facilitation	Reach, Adoption, Implementation
Fund & contract	Research Team (project budget)	Provide initial funding support for *Turtle Island Tales* in each community	SNAP-Ed Program Implementors, Administrators	Pre-implementation	Once	*Inner setting;* Implementation climate, compatibility, available resources *Outer setting; external policy and incentives*	Adoption, Implementation

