Facilitation to support initial implementation and sustainment	Research Team, CITs	Community-specific problem solving, budget, development, and submission support specific to SNAP-Ed and other available resources	SNAP-Ed Program Implementors, Administrators	Pre-implementation, Implementation, Sustainment, Scale out	Ongoing, monthly, 5 years	*Inner setting;* Implementation climate, compatibility, available resources *Implementation Process;* Planning, executing, reflecting & evaluating	Reach, Implementation, Maintenance (program)
Develop and implement tools for quality monitoring	Research Team, CITs, PSC	Use SNAP-Ed systems to create ongoing monitoring of implementation and outcome measures	SNAP-Ed Program Implementors, Administrators	Pre-implementation, Implementation, Sustainment, Scale out	Ongoing in PSC & CIT meetings (5 years)	*Inner setting;* Implementation climate *Outer setting; external policy and incentives*	Implementation, Maintenance (program)

*Acronyms:*
*CAIRHE* Center for American Indian and Rural Health Excellence, *CEDI* Community Engaged Dissemination and Implementation, *CFIR* Consolidated Framework for Implementation Research, *CIT* Community Implementation Team, *PSC* Project Steering Committee, *RE-AIM* Reach, Effectiveness, Adoption, Implementation, and Maintenance Framework, *SNAP-Ed* Supplemental Nutrition Assistance Program Education

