**RE-AIM measures**			
Reach	Number/proportion of Native American families in persistent poverty areas who receive *Turtle Island Tales;* representativeness based on race, ethnicity, economic status	Number of kits delivered	Research Team
Adoption	Number/proportion of Native American communities within given state that deliver *Turtle Island Tales; r*epresentativeness based on communities in persistent poverty areas	State-level reports	SNAP-Ed
Implementation: *Fidelity*	Proportion *Turtle Island Tales* toolkits delivered as planned	Monthly checklist with CITs	Research Team
Implementation: *Cost*	Material costs; implementation time; ongoing costs	Monthly checklist with CITs	Research Team
Maintenance	Funding stability; administrative support; partnerships; organizational capacity	CIT survey; Program Sustainability Assessment Tool	Research Team

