## Analysis

To assess program reach, we will track the number and proportion of families enrolled in *Turtle Island Tales* across participating communities. Representativeness will be evaluated using odds ratios (90% confidence interval) comparing enrolled families to relevant community census data (e.g., poverty status, age, sex). Recruitment rates will be analyzed using the number of families exposed to recruitment as the denominator, with time to enrollment of 25 and 50 families calculated per site. Differences in enrollment success across recruitment strategies will be assessed using the *prop.test *function in R, and community-level reach trends will be visualized relative to the timing of strategy implementation. Qualitative data from meetings and monthly feedback surveys will undergo descriptive content analysis [26], with transcripts double-coded in NVivo by two trained coders. In addition to descriptive content analysis, all Project Steering Committee and Community Implementation Team meetings will be transcribed with coding guided by CFIR and RE-AIM. This will allow the research team to summarize thematic content efficiently, identify emerging patterns across sites, and generate community-oriented recommendations.

To evaluate adoption, implementation, and maintenance, we will apply a convergent mixed methods approach, combining quantitative predictors from the CFIR and RE-AIM frameworks with qualitative data collected in an ongoing, parallel manner. Both data types will be equally valued, and mixed methods analysis will follow established implementation research procedures [27]. Quantitative analysis will include a descriptive summarization of CFIR domains over time and across sites, with pairwise comparisons to assess changes. Short-term budget impact analysis will capture costs associated with adoption and implementation during the study period. To project long-term sustainability, we will forecast five-year budgetary trends using the Bureau of Labor Statistics Employment Cost Index for staff costs and the Consumer Price Index for material and mailing costs. Community Implementation Team members will report on hours spent on implementation tasks (excluding research-specific activities). Personnel costs will be estimated using market-based salaries, and material costs will be based on invoices. Trendlines for anticipated cost growth will be developed to support planning for future program delivery.

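### As written, personnel cost for the budget impact draws on Community Implementation Team hours, although the Research Team distributes the kits and gives technical assistance, so staff cost is likely understated

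*Protocol article*

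**What the plan says.** The third aim in Project objectives is "determining the short- and long-term budget impact of integrating" the program into routine delivery.

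Two places in the protocol article fix where staff hours come from:
- Analysis: "Community Implementation Team members will report on hours spent on implementation tasks (excluding research-specific activities"). Hours are priced at market salaries and materials from invoices.
- Table 2, cost row: the measure is "Material costs; implementation time; ongoing costs" and the source is "Monthly checklist with CITs". The Research Team appears in that row as the collector of the data.

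Study design and setting describes who sits on these teams: "We anticipate that each Community Implementation Team will include local SNAP-Ed agents, tribal partners, and other community representatives". The Research Team is not listed.

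Table 1 assigns the work. For "Centralize distribution and technical assistance (dissemination organization"), the sole actor is the Research Team. The dose is monthly, with technical assistance as needed, and the timing covers implementation, sustainment and scale-out. For facilitation, the actors are the Research Team and the Community Implementation Teams, with dose "Ongoing, monthly, 5 years".

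For the long term, Analysis says "we will forecast five-year budgetary trends using the Bureau of Labor Statistics Employment Cost Index for staff costs", with the Consumer Price Index applied to materials and mailing.

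**The concern.** The people named as reporting hours are not the people Table 1 names as doing the central delivery work. Mailing a monthly kit is the core of this intervention. Assembling and dispatching kits and supporting local teams are delivery tasks, so the exclusion of research-specific activities does not explain why this labor has no stated source.

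The Discussion says the aim is a program that can be kept going after external research support ends. That is the moment at which Research Team delivery labor has to be paid for by someone else, bought in or replaced. A budget figure without it would be too low for an agency planning on it. Delivery is also staggered over several years, and hours that are not logged at the time are hard to reconstruct later.

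**Working it through.** The article states no hours, cost or budget figure, so there is none to reproduce. The check has three parts.

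**1. Task against source of hours**
- Kit distribution and technical assistance: done by the Research Team alone (Table 1); no stated source of hours.
- Facilitation: done by the Research Team and the Community Implementation Teams (Table 1); the stated source covers only the local teams' part.
- Local implementation tasks: done by the Community Implementation Teams; covered by Analysis and Table 2.
- Materials and mailing: materials are costed from invoices, and both are forecast with the Consumer Price Index; covered.

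The gap is thus Research Team delivery labor, not the whole cost of mailing.

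**2. Possible size**

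From the documents: up to 50 families per site in the first year (Participants) and 12 monthly kits per family (Intervention description), so at most 50 × 12 = 600 kits per site-year.

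Assumed, because the documents give nothing: 5 to 20 minutes of handling per kit; 2 to 8 Research Team hours per month on technical assistance and facilitation; 120 to 480 Community Implementation Team hours per site-year (C).

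Research Team hours: R = 600 × minutes / 60 + 12 × monthly hours.
- Low: 600 × 5/60 + 12 × 2 = 50 + 24 = 74 hours.
- High: 600 × 20/60 + 12 × 8 = 200 + 96 = 296 hours.

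Share of delivery hours unrecorded: R / (R + C).
- Smallest: 74 / (74 + 480) = 0.134, about 13%.
- Largest: 296 / (296 + 120) = 0.712, about 71%.

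With kit handling alone, leaving out technical assistance and facilitation, the range is 50 / (50 + 480) = 9% to 200 / (200 + 120) = 63%.

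These are shares of hours. They equal shares of staff cost only if both groups are priced at the same rate.

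**3. What the forecast does with the gap**

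Let S be true base-year staff cost, m the share missed and g the yearly growth of the Employment Cost Index. The recorded forecast in year t is (1 − m) × S × (1 + g)^t and the true one is S × (1 + g)^t. Their ratio is 1 − m in every year, whatever g is.

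Illustration with assumed m = 30% and g = 3%: the sum of 1.03^t for t = 1 to 5 is 5.468, and 0.30 × 5.468 = 1.64. So 1.64 base-year staff budgets would be missing over five years.

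For total cost, the understatement is the staff share times m. With staff assumed at 30% to 70% of total cost and m at 10% to 50%, it runs from 0.30 × 0.10 = 3% to 0.70 × 0.50 = 35%.

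**The case against.** The strongest reply is that silence is being read as exclusion. Analysis says the short-term budget impact will capture adoption and implementation costs, and the sentence on market salaries is not restricted to local team members. External partners need an instrument for reporting hours, whereas the way a research team records its own time may sit in a fuller protocol. This stands in part: that other hours are left out is an inference, and a reader who concludes that Research Team labor is definitely never captured goes beyond the text. But the article does name its sources of hours, twice, and both times they are the local teams. That mismatch with Table 1 is more than brevity.

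Second, Table 1 labels central distribution as a dissemination organization. An agency might in future buy assembled kits with handling labor in the price. That is possible and would shrink the gap, but no passage says that an invoice includes labor.

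Third, facilitation is shared, and the CEDI strategies section lists it among strategies still to be discussed and selected. This also stands: only the Research Team's part can be missed, and its amount is open. Central distribution, by contrast, is one of the three bundles proposed in advance, so the point does not depend on facilitation.

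A reader might also infer that the forecast is wrongly built because it mentions neither the number of families nor a split of start-up from recurring cost. The documents do not support that as a fault. Table 2 lists ongoing costs as an item, Analysis separates the short-term analysis from the forecast, and the remaining modeling detail may be left to a fuller plan.

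**Conclusion.** The point holds as a mismatch between who delivers and whose hours are collected. As written, the personnel cost for Aim 3 does not include Research Team delivery labor, so staff cost is likely understated, and indexing repeats the same proportional shortfall in each forecast year.

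The size cannot be derived from the documents. The range of about 13% to 71% of delivery hours rests on the 600-kit ceiling and on assumed handling, support and team hours. It shows that the gap could be modest or large, and it would be smaller if an invoice bundles handling.

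A reader might take this as a flaw that undermines the study. It does not: reach is the primary outcome and is unaffected, and budget impact is one of four aims in a descriptive case study. This should be fixed; confidence is moderate.

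**What to change.** - Have Research Team staff log their non-research hours on kit assembly, mailing, technical assistance and their part of facilitation in the existing monthly checklist.
- Price these hours at the same market-based salaries and show them as a separate line. If an invoice already includes handling labor, say so and do not count it twice.
- State the payer perspective of the budget impact analysis: whose budget is meant, and who is assumed to carry central distribution after the project.
- Report the budget impact and the five-year forecast with and without the Research Team line.

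The cost is a few minutes of logging per month and a few sentences of analysis text. The stated cost of the program will look less favorable. Logging should start as early as possible, because past hours can be recovered only by recall.

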## Discussion

This study addresses the critical need to understand implementation of culturally relevant, evidence-based interventions to prevent obesity and reduce cancer risk in Native American communities, particularly those experiencing persistent poverty. The "Delivery of *Turtle Island Tales* to Promote Family Wellness" study leverages innovative CEDI strategies to promote broad reach and sustainable implementation within SNAP-Ed systems across four states. Although childhood obesity prevention is recognized as a strategy to reduce lifetime cancer and chronic disease risk, few interventions have been developed to reflect the unique cultural and contextual realities of Native American families or to reach them at scale. Successful implementation often depends on trusted community champions—for example, respected elders—and tailoring materials to specific language and cultural contexts.

This study employs rigorous, theory-driven methods, including the RE-AIM and CFIR frameworks, to systematically address barriers and evaluate implementation processes across multiple ecological levels. A novel feature is the introduction of a mailed intervention approach within SNAP-Ed programming, which represents a significant departure from the direct education methods typically employed by SNAP-Ed. Given changes in service delivery following COVID-19, SNAP-Ed agents have expressed strong interest in expanding this model to increase program reach and sustainability. Moreover, tracking the dynamic nature of implementation strategy use with the LISTS method is a novel contribution that will rigorously evaluate the complex CEDI process. These CEDI strategies primarily focus on the CFIR construct of intervention characteristics, including the intervention source, compatibility with SNAP-Ed delivery systems and participant lifestyles, low implementation complexity, and relative advantage. Through detailed tracking of implementation strategies and corresponding CFIR constructs, we plan to identify how specific mechanisms, such as improved cultural compatibility, increased perceived relative advantage, and reduced complexity, contribute to improvements in RE-AIM outcomes with a primary focus on reach. These hypothesized mechanisms are expected to guide understanding of how contextually aligned CEDI strategies lead to improved RE-AIM outcomes of *Turtle Island Tales*.

In consultation with our community and SNAP-Ed partners during the study planning phase, we considered alternative designs, including randomization of communities to different implementation strategies or quasi-experimental comparisons but determined these approaches were not feasible. Limited foundational knowledge exists about which CEDI strategies are most effective for scaling out obesity prevention interventions in Native American communities, and delaying program support could discourage future program adoption. SNAP-Ed programs and community partners with interest in *Turtle Island Tales* are unlikely to accept assignment to waitlist or comparison conditions, given competing demands and pressing community needs. Thus, a pragmatic, mixed-methods case study design was selected to both advance implementation science and support timely, meaningful local impact. Although analytic approaches such as Cox hazard models were considered to examine differences in reach, they were deemed inappropriate given the non-randomized, partner-driven design and anticipated sample sizes.

An important contextual consideration for this study is the budgetary limitations inherent in SNAP-Ed and other public health programs. Within SNAP-Ed, allowable costs are typically directed to direct education efforts, with minimal resources for indirect education, capacity building, or maintenance activities. Consequently, identifying cost-effective, adaptable implementation strategies is critical for ensuring that interventions like *Turtle Island Tales* can be maintained once external research support concludes, particularly given that so few culturally relevant interventions are available for young Native American children. This project addresses these realities by embedding cost-tracking and sustainability planning across all phases of implementation, with the goal of producing practical, scalable solutions for programs operating in rural/frontier and persistent poverty areas.

Moreover, the “Delivery of *Turtle Island Tales* to Promote Family Wellness” study will systematically document and characterize culturally and locally tailored CEDI strategies. Because they will be co-produced with community partners, these strategies are expected to influence health outcomes across varied settings and enhance understanding of how to support long-term program success in real-world environments. The project’s conceptual framework integrates social ecological, dissemination and implementation, and behavioral theories, offering a model for addressing health promotion that is responsive to the lived experience of Native families. Further, the use of convergent mixed methods will enable us to examine cross-site variation in implementation, propose adaptable versus core components of CEDI strategies, and inform generalizability of findings to other Native American and rural communities.

Despite co-production of CEDI strategies and ongoing support, it is possible that some communities may face unanticipated barriers to adoption, implementation, or sustainment. Factors such as staff turnover, shifting administrative priorities, or competing local initiatives may affect program continuity. Our study design accounts for this by documenting site-specific adaptations and progress, which are critical to refining our CEDI strategy toolkit for future applications. Our findings will directly inform the development of a Native American-specific CEDI strategy toolkit and an implementation research logic model to support the long-term Delivery of *Turtle Island Tales* and similar interventions aimed at health promotion and disease prevention. Ultimately, outcomes from this study aim to guide future efforts to adapt, scale, and sustain culturally grounded interventions across a broader range of communities and SNAP-Ed systems nationwide, contributing to efforts to strengthen public health infrastructure and intervention impact.

